## Abstract

**Aim::**

The Pain Recognition and Evaluation to Validate Effective Neck and back Treatment (PREVENT) study aims to identify cognitive, behavioral, and treatmentrelated predictors of chronic musculoskeletal pain (CMP) development following emergency department (ED) care for acute neck or back pain after trauma.

**Background::**

CMP is a leading cause of global disability, yet early risk factors for its development remain poorly characterized, particularly in ED settings. This prospective observational study will recruit 246 adult patients presenting with acute (≤ 4 weeks) neck or back pain after a recent trauma. Pain beliefs – measured using pain and attitude questionnaires – serve as the primary independent variable. Mediating variables include catastrophic thinking, fear-avoidance behaviors, low physical activity, poor recovery expectations, and low self-efficacy for pain management. Covariates include demographics, social determinants of health, mental health disorders, and high-risk substance use. The primary outcome is the presence of CMP at six months, defined as pain on most or every day for at least three months. Participants will complete follow-ups at 1, 3, and 6 months. Multivariable logistic regression, mediation analyses, and interaction testing will explore effects of pain beliefs on CMP development. As a secondary aim, a subset of participants will complete Think Aloud cognitive interviews to assess response process validity for the Neck Pain Attitudes Questionnaire (Neck-PAQ), a region-specific adaptation of the Back Pain Attitude Questionnaire, analyzed using a deductive content analysis framework.

**Discussion::**

This study is among the first to investigate the cognitive and behavioral predictors of pain chronification in the ED. Ethical approval has been obtained from The George Washington University Institutional Review Board. Findings will inform the design of targeted, ED-based screening and intervention strategies, including adaptation of a pain-specific Screening, Brief Intervention, and Referral to Treatment (SBIRT) model. Results will be disseminated through peer-reviewed publications, conferences, and stakeholder engagement.

## Introduction

Chronic musculoskeletal pain (CMP) is the leading cause of disability worldwide, affecting millions annually and imposing an economic burden of $560–635 billion in the U.S. alone (Vos *et al.*, 2020; Gaskin & Richard, 2012). CMP, characterized by persistent or recurrent pain in the muscles, bones, joints, or tendons, most commonly affects the neck and lower back regions (Treede *et al.*, 2015; World Health Organization, 2022). Emergency departments (EDs) frequently serve as the initial point of care for individuals experiencing either acute or chronic pain, with musculoskeletal pain-related complaints representing the fourth most common reason for ED visits in 2021 (9.5 million cases) (Centers for Disease Control and Prevention, 2023).

Despite the ED’s important role in addressing pain across the acute-chronic continuum, limited research has examined ED-specific risk factors contributing to the transition from acute to chronic pain, and few interventions have been systematically implemented to prevent this trajectory. In the general population, the annual incidence of chronic pain is 6.3% (Nahin *et al.*, 2023), but among ED patients with acute pain, the risk of chronic pain transition is substantially higher, ranging from 12%–27% (Beaudoin *et al.*, 2020; Office of the Assistant Secretary for Planning and Evaluation, 2021; Bourassa *et al.*, 2020; Barnett *et al.*, 2017), underscoring the ED as a critical setting for early identification and prevention. Prior ED-based studies have identified predictors such as pain intensity, body region, and opioid use (Beaudoin *et al.*, 2020; Office of the Assistant Secretary for Planning and Evaluation, 2021; Bourassa *et al.*, 2020; Barnett *et al.*, 2017), but the role of maladaptive pain beliefs, kinesiophobia, pain catastrophizing, and guideline-discordant care remains largely unexplored. Evidence from post-surgical and outpatient populations has established that these psychological factors and guideline-discordant care (e.g., excessive imaging) are associated with an increased risk of developing chronic pain (Theunissen *et al.*, 2012; Stevans et al., 2020), and this is further supported by observational and conceptual studies linking these factors to pain persistence, negative affect, and pain-related disability (Rogers & Farris, 2022; Coninx *et al.*, 2025; Ray *et al.*, 2022; Keller *et al.*, 2023; Brown *et al.*, 2020; Vivekanantha *et al.*, 2023). However, their potential value in ED-based screening and intervention remains untested.

The overarching goal of this study is to determine whether maladaptive pain beliefs, fear-avoidance behaviours, catastrophizing, and guideline-discordant care contribute to the transition from acute to chronic pain among ED patients with acute post-traumatic musculoskeletal pain. We hypothesize that individuals who transition to CMP will exhibit greater psychological distress (e.g., anxiety, depression, pain catastrophizing), misinformed pain beliefs (e.g., kinesiophobia), higher rates of non-prescribed psycho-active substance use (e.g., alcohol, marijuana), and distinct patterns of ED-based pain management (e.g., increased imaging and pharmacologic interventions).

To guide our study design and selection of predictors, we developed a conceptual framework titled the Cognitive Risk Model for CMP (Figure 1). Grounded in the fear-avoidance and biopsychosocial models (Vlaeyen *et al.*, 2016; Engel, 1977), this framework posits that maladaptive pain beliefs influence chronic pain development through psychological and behavioural pathways. It is further informed by emerging affordance-based theories of pain, which suggest that persistent pain alters perceived opportunities for action (i.e. affordances), reinforcing avoidance behaviours (Coninx *et al.*, 2025). This theoretical lens highlights the importance of addressing cognitive and behavioural responses to acute pain early in the care trajectory. The study aims to test this framework in an ED setting, with the goal of identifying individuals at heightened risk of chronic pain development and informing future early intervention strategies.

**Figure 1. f1:**
[figure not shown]
Cognitive Risk Model for Chronic Musculoskeletal Pain. This directed acyclic graph (DAG) illustrates hypothesized pathways through which pain beliefs influence the development of chronic musculoskeletal pain (pain frequency) following an ED visit. Psychological and behavioural mediators (grey), confounding variables (white), and primary outcome (blue) are shown, with arrows representing theorized causal relationships.

## Methods and analysis

### Conceptual framework & analytic rationale

Building upon the framework described above, the Cognitive Risk Model for CMP conceptualizes pain beliefs and attitudes as the primary independent variable, with the presence of CMP as the primary outcome, and functional status and pain intensity as secondary outcomes. By applying this theoretical lens, our study aims to identify how pain beliefs and behavioural responses constrain meaningful action and contribute to pain persistence. This model informed the selection of variables, timing of follow-up assessments, and the structure of our analytic approach. Specifically, it supports the inclusion of psychosocial and behavioural mediators (e.g., catastrophizing, fear-avoidance, physical activity, pain self-efficacy, recovery expectations), and contextual modifiers (e.g., substance use, social determinants of health, mental health conditions), and pathway modelling to explore both direct and indirect effects.

The study design was further refined and strengthened through consultation with ED clinicians, pain researchers, and a patient partner with lived experience of chronic pain, ensuring alignment with clinical priorities and patient-centred outcomes.

Recruitment will occur through direct, in-person approaches in the ED based on screening via the electronic medical record (EMR) tracking system (Figure 2).

**Figure 2. f2:**
[figure not shown]
Study Flowchart. Flowchart outlining the PREVENT study procedures for participant screening, enrolment, and follow-up. Potential participants are identified through electronic medical record pre-screening, followed by in-person eligibility assessment and informed consent. Enrolled participants complete baseline forms and are followed at 1-, 3-, and 6-month intervals, with chart audits conducted at the 1- and 6-month time points. Screening logs are completed for all screened individuals regardless of eligibility or consent status.

### Inclusion criteria

Adult ED patients ≥18 years of age will be eligible for participation if they meet specific criteria: (1) have acute neck and/or low back pain (onset ≤4 weeks); (2) have incurred a recent (≤4 weeks) trauma (e.g., motor vehicle crash, falls, bicycle accidents); (3) have no definitive cause of pain related to unstable fracture, malignancy, active infection, or inflammatory conditions (e.g., ankylosing spondylitis); (4) have no co-occurring progressive neurological symptoms (e.g., spinal cord injury or cauda equina syndrome); (5) are not currently pregnant or planning pregnancy within the next 6 months; (6) have no impairments precluding informed consent (e.g., cognitive dysfunction); (7) are English-speaking; and (8) have a willingness to participate in follow-up assessments.

The ≤4-week trauma window ensures that participants are enrolled during the acute phase of pain and that pain onset can be clearly linked to a specific inciting event. This design feature enhances the precision of prospective tracking of pain progression and aligns with established chronic pain definitions, which require symptoms to persist for ≥3 months on most days or every day (Dahlhamer *et al*., 2018; Nahin *et al.*, 2023; Ray *et al.*, 2024). This approach also mirrors methodologies used in post-surgical pain studies, where researchers follow patients from a well-defined index event to assess long-term pain outcomes (Katz & Seltzer, 2009). By anchoring enrolment to a recent traumatic event, we minimize misclassification of subacute or chronic pain and increase the validity of modelling. This approach is consistent with prior ED-based longitudinal research (Beaudoin *et al.*, 2020) and supports reliable identification of acute-to-chronic pain transitions.

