The primary outcome is the development of CMP in the neck and/or low back, defined as pain in the same anatomical region as the acute presenting complaint, present on most days or every day for at least three months. Secondary outcomes will include changes in pain beliefs (assessed through B-PAQ/N-PAQ scores), pain catastrophizing (PCS scores), and fear-avoidance behaviours (TSK scores), and healthcare utilization, including recurrent ED visits and outpatient care. Additional secondary measures will evaluate changes in physical activity levels (IPAQ-SF scores), pain self-efficacy (PSEQ-2 scores), and pain-related disability, measured through changes in ODI and NDI scores over time. While this study applies the Cognitive Risk Model for CMP specifically to post-traumatic neck and/or low back pain, the model is designed to be adaptable to other anatomical regions and chronic pain types – including both chronic primary and secondary musculoskeletal pain – in future research (Treede *et al.*, 2015).

In addition to baseline enrolment forms, we will perform a chart audit post-ED discharge to assess ED management, including ED imaging (x-ray, CT, MRI), medication management (including opioids, NSAIDs, acetaminophen, and muscle relaxants), ED disposition (admission vs discharge), diagnostic codes (ICD-10 for musculoskeletal and neurological conditions), and referrals provided (e.g., primary care, pain specialist, physical therapy). After 1- and 6-month follow-ups, additional audits will be completed utilizing an automated process to query the EMR using the Financial Identification Number (FIN) and Medical Record Number (MRN) from the index ED visit. Using these patient-specific identifiers collected during enrolment, a report can be generated for pre-specified data fields in the EMR which exactly matches the data dictionary in the case report form (CRF) built in REDCap. Data can be imported into REDCap and will be checked for fidelity and missingness. An advantage of this process is reduction in bias inherent in manual chart review (Gilbert *et al.*, 1996). As a further check, we will query the regional health information exchange for relevant healthcare utilization at regional outside hospitals.

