### Sample size & quantitative data analysis

Our primary outcome – pain frequency – is assessed as a categorical variable based on participants’ reported number of days per week experiencing neck or low back pain (0–1 days, 2–3 days, 4–5 days, or 6–7 days). Pain frequency will be assessed at 1, 3, and 6 months. For analysis, responses will be dichotomized to classify CMP status: participants reporting pain on 4–5 or 6–7 days per week will be categorized as having CMP (coded as 1), while those reporting 0–1 or 2–3 days per week will be categorized as not having CMP (coded as 0). Based on prior studies reporting a 12%–27% transition rate from acute to chronic pain (Beaudoin *et al.*, 2020; Office of the Assistant Secretary for Planning and Evaluation, 2021; Bourassa *et al.*, 2020; Barnett *et al.*, 2017), we conducted a power analysis to estimate the incidence of CMP with acceptable precision. Using a small effect size (Cohen’s d 0.2), with α = 0.05 and power = 0.80, a minimum sample size of 197 participants is required. To account for an estimated 25% attrition rate, we will recruit 246 participants to ensure adequate study power. This sample size will also provide sufficient power to explore the association between baseline pain beliefs and subsequent development of CMP, as well as to conduct preliminary analyses for establishing potential clinical cut-offs on pain relief measures. Higher scores may indicate individuals at elevated risk for developing CMP and who may benefit from targeted educational interventions. However, these exploratory analyses will require validation in independent samples.

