## Discussion

Musculoskeletal pain – particularly in the neck and lower back – is the leading cause of disability worldwide and a frequent reason for ED visits (Vos *et al.*, 2020; World Health Organization, 2022; Centers for Disease Control and Prevention, 2023). Despite its high in acute care settings, few studies have systematically investigated early predictors of chronicity or developed target interventions during this critical window. The Pain Recognition and Evaluation to Validate Effective Neck and back Treatment (PREVENT) study addresses this gap by prospectively evaluating cognitive, behavioural, and contextual factors that may contribute to the transition from acute to chronic pain following traumatic injury.

Chronic pain affects approximately 1 in 4 adults and 1 in 5 children, contributing to increased rates of co-morbid health conditions and increased mortality risk. (Dahlhamer *et al*., 2018; Chambers *et al.*, 2024; Foley *et al.*, 2021; Ray *et al.*, 2024). Individuals with chronic pain experience double the risk mortality compared to those without, and those with high-impact chronic pain – defined as chronic pain that limits life or work activities – face a 2.5-fold increased risk (Dahlhamer *et al*., 2018; Ray *et al.*, 2024). Among individuals living with chronic pain, an estimated 8%–12% meet criteria for opioid use disorder, and many also have elevated odds of other substance use disorders (Vowles *et al.*, 2015; Havlik *et al.*, 2024). Early identification of high-risk individuals, coupled with scalable, evidence-based interventions, is essential to interrupt this trajectory. Findings from this study may inform ED-based strategies to reduce the incidence of CMP, improve long-term health outcomes, and decrease healthcare utilization and opioid-related harms.

One promising framework is the Screening, Brief Intervention, and Referral to Treatment (SBIRT) approach, which has been successfully applied to substance use and mental health conditions but has not yet been adapted for acute pain management (Barata *et al.*, 2017; Hargraves *et al.*, 2017). In musculoskeletal pain scenarios, guideline-concordant care emphasizes a person-centred approach that includes education, shared decision making, and supported self-management (Lin *et al.*, 2020; Hutting *et al.*, 2022).

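### Eligibility dates the presenting pain and the trauma but does not establish freedom from chronic neck or low back pain before the injury, so some existing cases can be counted as newly developed CMP

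*Protocol article*

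**What the plan says.** The Inclusion criteria section lists eight conditions. Two concern timing: patients must "have acute neck and/or low back pain (onset ≤4 weeks", and must "have incurred a recent (≤4 weeks) trauma (e.g., motor vehicle crash, falls, bicycle accidents". A third removes specific pathology: patients must "have no definitive cause of pain related to unstable fracture, malignancy, active infection, or inflammatory conditions (e.g., ankylosing spondylitis". The others concern progressive neurological symptoms, pregnancy, capacity to consent, language and willingness to be followed. None mentions neck or low back pain before the injury.

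The same section gives its reason for the trauma window: "By anchoring enrolment to a recent traumatic event, we minimize misclassification of subacute or chronic pain and increase the validity of modelling".

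The outcome is described in two ways. Under Quantitative outcomes & assessment tools, the primary outcome is the development of CMP, "defined as pain in the same anatomical region as the acute presenting complaint, present on most days or every day for at least three months". Under Sample size & quantitative data analysis, CMP is coded from the "number of days per week experiencing neck or low back pain", with 4 to 7 days a week coded 1. That coding refers neither to the index region nor to pain status before the injury.

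Table 1 lists the NHIS chronicity item at months 0, 1, 3 and 6 as the primary outcome measure. The analysis section names only months 1, 3 and 6. Past medical history is collected at month 0 as a covariate.

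**The concern.** The study wants to estimate and predict a transition from acute to chronic pain. Only someone who does not already have the outcome can make that transition. Anchoring to a trauma dates the index event, but it says little about the pain history behind it.

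Two kinds of participant could enter with the outcome, or something close to it, already present:

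- **Same region.** A patient with long-standing neck or back pain has a new flare there after a fall or crash. Whether this pain counts as having its onset within four weeks is left to the screener.
- **Other region.** A patient has new neck pain and long-standing low back pain. The same-region definition would not count the old back pain. The days-per-week coding, as worded, would.

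Two results are exposed. The reported rate of developing CMP rises, because existing cases enter both numerator and denominator. The association between baseline beliefs and CMP can also be distorted, because prior chronic pain plausibly shapes beliefs and also predicts frequent pain at six months. The exploratory ROC cut-offs on belief scores use the same outcome and would inherit the problem.

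**Working it through.** **The plan's own figures.** The stated 197 reproduces as a one-sample, two-sided normal calculation: ((1.960 + 0.842) / 0.2)² = 196.2, rounded up to 197. The 246 is 197 × 1.25 = 246.25. The point does not depend on either number. I use 197 only as a yardstick for sampling error.

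**Inputs from the protocol.** Expected transition rate p = 12% to 27% (sample size section).

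**Inputs assumed, because the documents give none.**
- q, the share of participants with chronic neck or low back pain before the injury that would be counted as CMP if it persists: 5% to 15%.
- r, the share of these coded as CMP at six months: 70%.
- δ, how much worse their baseline beliefs are: 0.5 SD. This is used only for the association.

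**Effect on the rate.** Observed rate = q·r + (1 − q)·p. Overstatement = q·(r − p), which is positive whenever r exceeds p. Share of counted cases that were already present = q·r / observed rate.

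| q | true p | observed rate | overstatement (points) | already present, share of counted cases |
|---|---|---|---|---|
| 5% | 12% | 0.035 + 0.114 = 14.90% | 2.90 | 23.5% |
| 5% | 27% | 0.035 + 0.2565 = 29.15% | 2.15 | 12.0% |
| 10% | 12% | 0.070 + 0.108 = 17.80% | 5.80 | 39.3% |
| 10% | 27% | 0.070 + 0.243 = 31.30% | 4.30 | 22.4% |
| 15% | 12% | 0.105 + 0.102 = 20.70% | 8.70 | 50.7% |
| 15% | 27% | 0.105 + 0.2295 = 33.45% | 6.45 | 31.4% |

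If r runs from 0.6 to 1.0 over the same q, the overstatement runs from 0.05 × (0.60 − 0.27) = 1.65 points to 0.15 × (1.00 − 0.12) = 13.2 points.

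**Against sampling error.** The 95% half-width at N = 197 is 1.96·√(p(1 − p)/197), which is 4.5 points at p = 12% and 6.2 points at p = 27%. With r = 70%, the bias is below sampling error at q = 5%. At q = 10% it is above at the lower rate and below at the higher. At q = 15% it is above at both. Unlike sampling error, it does not shrink with more recruitment.

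**Effect on the association.** Suppose beliefs have no effect among participants with prior pain, and none among those without. Before adjustment, the log odds ratio per SD is approximately δ × [share with prior pain among cases − share among non-cases].
- q = 15%, p = 12%: the share among non-cases is 0.15 × 0.30 / 0.793 = 0.057. Then 0.5 × (0.507 − 0.057) = 0.225, an OR of about 1.25.
- q = 5%, p = 27%: the share among non-cases is 0.05 × 0.30 / 0.7085 = 0.021. Then 0.5 × (0.120 − 0.021) = 0.0495, an OR of about 1.05.

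Adjusting for prior pain status returns the OR to 1, because by construction beliefs and outcome are unrelated within each group.

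**The case against.** The strongest reply is that the plan already excludes most of these patients. Pain that was continuously present in a region before the injury did not begin within four weeks, so a strict reading of the onset criterion bars it. The stated intent is to limit misclassification of chronic pain, and the treating ED provider helps confirm eligibility. The outcome definition is restricted to the index region, so old back pain in a patient with a neck injury should not count. Month-0 pain frequency and medical history are collected, and sensitivity analyses under alternative definitions are planned.

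Much of this stands. A reader might infer that eligibility does nothing to remove pre-existing chronic pain, and the onset criterion does not support that. The other-region example arises only if the days-per-week coding is applied as worded, since the same-region definition contradicts it.

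A reader might also apply the Discussion's statement that "Chronic pain affects approximately 1 in 4 adults and 1 in 5 children" to this sample. That figure is for chronic pain at any site in the general population, not neck or low back pain in patients who have passed an onset and trauma screen.

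Nor does it follow that a medical-history covariate is useless. If it captures prior spinal pain, adjustment can deal with the confounding. It cannot correct the rate, whose numerator and denominator still include people who already had the outcome.

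What the reply does not close is acute-on-chronic pain in the same region, which the criteria leave undecided and the same-region rule cannot remove. The month-0 item and the medical history are given no role in defining who is at risk. A month-0 answer about current days per week would describe the acute episode, not the period before the injury.

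**Conclusion.** The point holds in limited form. The criteria do not establish that participants were free of chronic neck or low back pain before the injury. Same-region acute-on-chronic pain is not clearly excluded, and other-region pain is counted if the coding in the sample size section is used as written.

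The direction of the effect on the rate is clear whenever people with prior chronic pain are more likely than others to be coded positive at six months. The size is unknown from the documents. With 5% to 15% affected and 70% persistence, both assumed, the rate is overstated by about 2 to 9 points, and 12% to 51% of counted cases were already present. If screeners apply the onset rule strictly and the same-region definition governs the coding, the affected share would be smaller, possibly close to zero.

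The spurious OR of about 1.05 to 1.25 per SD also assumes beliefs 0.5 SD worse in the affected group and no adjustment for prior spinal pain. It is a risk of confounding that adjustment can address, not an unavoidable bias. The matter should be settled while enrolment is still early.

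**What to change.** The eligibility list can stay as it is. The changes concern one baseline item, the analysis set and the coding.

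1. At month 0, word the NHIS item already in Table 1 so that it also asks about the three months before the injury, separately for neck and low back.
2. Define the primary at-risk set as participants without pain on most days or every day in the index region over that period. Report the others separately.
3. Carry the same-region rule from the outcome definition into the days-per-week coding, so that the two sections agree.
4. As a sensitivity analysis, fit the belief model in all participants with adjustment for prior spinal pain.
5. For participants already enrolled (25 when the article was written), take prior pain from the EMR history or ask at the next contact.

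The cost is one reworded item, some recall error about the pre-injury period, and a smaller primary set. With 246 × 0.75 = 184.5 completers, a 5% to 15% share is about 9 to 28 participants. That is an upper figure, since those whose prior pain was only in the other region stay in the at-risk set.
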